### Relevant concomitant care permitted or prohibited during the trial {11d}

There are no limits on the concomitant care that patients can receive during the RCT, as long as the participant meets the inclusion criteria. Usual care continues for both trial arms.

### Provisions for post-trial care {30}

Participants in the intervention arm have access to the web-app component of the intervention for the 18 months they are within the trial.

As we hope to secure funding for longer term follow-up (e.g. to examine effects of the intervention on adherence at 5 years), we decided not to use a wait list control design (i.e. one which permits access to the intervention for usual care participants after the trial is completed).

### Outcomes {12}

Two primary outcomes are assessed: (i) poor AET adherence and (ii) cancer-specific HRQoL. Adherence is measured using a combination of an objective measure (proportion of days covered (PDC) based on prescription encashment data^1^ routinely recorded by the NHS from community pharmacy records) and a subjective measure (self-report using MARS-5 [31]) over 18 months post-randomisation. Combining objective and subjective measures of adherence is considered the gold standard approach and allows misclassification to be reduced [45]. Participants will be classified, for analysis, as showing some degree of non-adherence (henceforth ‘inadequately adherent’; (PDC < 80%) OR (PDC ≥ 80% and a total MARS-5 score of ≤ 23)) or ‘adequately adherent’ (PDC ≥ 80% AND a total MARS-5 score of > 23) [46]. Cancer-specific HRQoL will be assessed using the FACT-G questionnaire [32]. Primary and secondary outcomes and potential mediators are specified in Table 1.

#### Health economic evaluation

Women complete the EQ-5D-5L [34] and report the resource use that they consider to be related to their breast cancer or side effects/complications at baseline, 6, 12, and 18 months. The resource use questionnaire was adapted from the UK Cancer Costs Questionnaire [47] and pre-tested among patients, clinicians and other members of the project team. AET costs will be based on prescription data. A within trial cost-utility analysis will estimate the cost per quality-adjusted life-year (QALY) gained. For HT&Me vs. usual care the base case analysis will take an NHS and personal and social services perspective; a sensitivity analysis will explore a societal perspective. EQ-5D-5L-related utilities, resource use and costs to the NHS, patients and society will be reported. Resource use and costs will be scaled-up to ascertain a national NHS cost/budget impact.

#### Process evaluation

Using a mixture of qualitative and quantitative methods, the process evaluation will explore fidelity of the intervention as delivered, received, and enacted; assess whether the intervention worked as hypothesized by the logic model; and identify any moderating contextual factors and/or unintended consequences of the intervention.

To maximise our understanding of usual care and contextual factors, sites are asked to complete a short questionnaire when they first join the study and at the end of recruitment to describe current practices in relation to any support routinely provided to women regarding endocrine therapy. As the trial is pragmatic and set against ‘real world’ practice, we do not plan to include this data in the statistical analysis related to the primary outcomes. Instead, this data will be considered descriptively within the mixed method process evaluation as it captures contextual issues that may influence, for example, the types of hospitals/services or patients for whom the intervention ‘works’.

To understand mechanisms of action of the intervention, structural equation modelling approaches will be used to estimate the proportion of the intervention effect on the primary outcomes that occurs via the putative mediator variables that are the target of the intervention (Table 1). This analysis will inform understanding of whether, and to what extent, the mediator variables were influenced by the intervention and, hence, how the intervention ‘worked’.

Semi-structured interviews will also be conducted during the trial with participants (intervention arm, *n* = 25–30; usual care arm, *n* = 25–30) and SWEET study practitioners and other key health professionals (*n* = 25–30). These will explore (as appropriate) the following: views and experiences of the intervention and the trial overall, as well as contextual factors. Furthermore, these interviews will explore what would need to be in place (i) to maintain the intervention as a part of routine care in the absence of the research team; and (ii) to provide the intervention to participants who do not speak English. Interviews will be analysed thematically using the Framework Approach [48].

Further to this, within the follow-up questionnaires (see Participant Timeline section), participants are asked for their opinions on how helpful they found the different components of the intervention.

Finally, bespoke anonymised web-app analytics are recorded to determine how often individual participants use the web-app and which elements or pages they access.

#### Longer term follow-up

Participants provide consent to be followed up for up to 15 years. They will be flagged through NHS databases, in the four nations, to identify hospital admissions (e.g. via Hospital Episode Statistics (HES) in England) and deaths (e.g. via Office of National Statistics mortality records in England). Separate funding will be sought for longer-term follow-up to assess adherence and breast cancer deaths, and survival, beyond the end of the current programme of research.

### Participant timeline {13}

The participant pathway can be seen in Fig. 2.

**Fig. 2 Fig2:**
[figure not shown]
The participant pathway

After providing consent, participants are asked to complete the baseline questionnaire, consisting of self-reported measures described in Table 1. This can be completed electronically, or in a paper format. Once complete, participants are randomised as described in the Sequence Generation section below. Those in group A participate in the HT&Me intervention, as described above. All participants are asked to complete a follow-up questionnaire at 6, 12, and 18 months, which repeat the questions from the baseline (follow-up questionnaires can be completed electronically, or in a paper format). A representative sample of participants from both groups will be invited to participate in process evaluation interviews as described above. Long-term follow-up (for up to 15 years) will be conducted via data linkage (dependent on additional funding). The Schedule of Assessments can be seen in Table 3 (Additional file).

### Recruitment {15}

Potentially eligible participants are either identified via multi-disciplinary team meetings, via hospital records or in hospital clinics. A member of the local team at each site reviews the potential participants’ medical records to assess eligibility. As previously described, a PIS is provided by the local research team, either in person or by post or email, and informed consent gained. All women considered potentially eligible and approached are added to site screening logs.

## Assignment of interventions: allocation

### Sequence generation {16a}

Local research teams at sites randomise each participant on the online automated SWEET randomisation portal, hosted by the SWEET trial office. Participants are randomised on a 1:1 basis to the HT&Me intervention plus usual care, or to usual care alone. The statistician checks the allocation intermittently to ensure randomisation is balanced across the trial arms. Trial arms are allocated randomly using a bespoke computerised minimisation algorithm held centrally at the SWEET trial office and stratified, in line with previous research [11, 17, 25] and recommendations from our Clinical Reference Group, as follows:

Age: < 50, 50 +AET type: tamoxifen/AITreatment complexity

i.No chemotherapy, no anti-HER2, no CDK4/6i.ii.Chemotherapy, no anti-HER2, CDK4/6i.iii.Chemotherapy, anti-HER2, no CDK4/6i.iv.Chemotherapy, no anti-HER2, no CDK4/6i.v.No chemotherapy, no anti-HER2, CDK4/6i.

### Concealment mechanism {16b}

Randomisation takes place via a secure automated link—thus the mechanisms of generating the allocation sequence and randomisation patterns are concealed from those doing the randomisation at the NHS site, as well as all other research team members.

### Implementation {16c}

After randomisation has been undertaken, the local research team inform the participant if they have been randomised to the intervention plus usual care arm, or the usual care alone arm.

## Assignment of interventions: blinding

### Who will be blinded {17a}

Not applicable—this is an unblinded trial. Our primary (and main secondary) outcomes are either patient reported (e.g. HRQoL/self-reported adherence) or objectively measured using health service data (e.g. PDC). Following a patient centred approach, for trial outcomes which were not assessed using objective health service data, we determined that these should be assessed by the patients themselves, rather than (for example) their clinicians. It was our intention to create an ‘environment’ where women would feel able to honestly report how they were feeling, and whether they had been taking their AET; therefore, we used self-completed PROMs rather than questionnaires administered by someone in the hospital or research team. As women knew which arm they were in, this was therefore unblinded.

### Procedure for unblinding if needed {17b}

Not applicable—this is an unblinded trial.

## Data collection and management

### Plans for assessment and collection of outcomes {18a}

Site staff are expected to collect key clinical information (including information about diagnosis, tumour histology, surgery, relevant planned adjuvant treatment) and demographic information at baseline using approved case report forms. Self-reported outcomes are collected from participants via questionnaire at baseline, 6, 12, and 18 months, as described above. All tools and scales within the questionnaires were previously validated or have been adapted from validated instruments to fit this specific context and patient group.

### Plans to promote participant retention and complete follow-up {18b}

All trial follow-up data can be collected remotely, to minimise participant burden and promote participant retention. Up to two reminders (by phone or email) to complete the follow-up questionnaires may be sent if needed. Where participants are deemed as lost to follow-up, data will continue to be collected remotely where possible using hospital records unless a participant explicitly withdraws their consent.

A dedicated email address will be provided to participants for support with any technical difficulties relating to the HT&Me web-app. All research contacts will aim to build a positive relationship and experience for participants.

### Data management {19}

SWEET uses electronic remote data capture (via the bespoke SWEET database). Data entered by site staff is reviewed by the SWEET trial office, with actions outlined in the data management plan to protect participant safety, compliance and the integrity of the data. In-built validations, agreed with the co-CIs and trial statistician, have been used within the database to reduce the risk of ineligible participants being recruited and illogical or incorrect data being entered. The trial manager (or delegate) will regularly produce reports to monitor data completeness and quality, and missing data or discrepancies will be raised with the relevant site.

Questionnaires can be completed by the participant directly either using an electronic questionnaire which populates into the trial database, or on paper if they prefer. All paper forms are returned to the SWEET trial office where they are entered onto the secure database by a member of the trial team—primarily the data entry clerk. The trial team will conduct ad hoc spot checks to double check entry. The paper forms are securely stored in order of trial number in locked filling cabinets in the secure trial office and are transferred to the secure archiving room once entered. The online system can be accessed by the trial team via individual login with access rights assigned accordingly. Ongoing data entry quality control checks are made at agreed intervals. All documents will be stored safely in confidential conditions as outlined below.

### Confidentiality {27}

The trial is conducted in accordance with the current UK General Data Protection Regulation, and participant anonymity is maintained throughout, and following completion of the trial. Participants are allocated a study specific trial number which is used to identify them on all trial documents and on the database. A full back up of the database is run every day, in additional to transactional backups every 15 min.

Participants consent to provide their name, NHS number (or devolved Nation equivalent), date of birth, GP and personal contact details (telephone number and email address). Access to this data is restricted to trial staff and authorised personnel only, this includes the central research team who are conducting the trial, overseeing HT&Me accounts and performing NHS (or other devolved Nation equivalent) data linkage, the BCN team (where BCN are responsible for conducting the SWEET consultations), and the research team responsible for conducting the process evaluation interviews. Trial data, including personal identifiable information, is securely stored on the SWEET database, developed and maintained by the Warwick Clinical Trials Unit Programming Team.

The HT&Me web-app is securely hosted online on Microsoft Azure (housed in the UK) with personal data stored within a two-layer encrypted folder. The information collected on use of the web-app (analytics) will be anonymous; IP addresses are not collected. Linked datasets obtained from NHS England (or devolved Nation equivalents) are pseudonymised and securely stored to enable analysis.

Process evaluation interviews will be audio-recorded. These, and any recordings of SWEET consultations, will be securely transferred from the recording device to a secure laptop and uploaded to the trial area on the secure server of the SWEET trial office. Recordings will then be deleted from their original source.

### Plans for collection, laboratory evaluation, and storage of biological specimens for genetic or molecular analysis in this trial/future use {33}

Not applicable—biological specimens are not collected.

## Statistical methods

### Statistical methods for primary and secondary outcomes {20a}

The data will be analysed in line with the statistical and health economics analysis plan, which will be reviewed and approved by the Data Management Committee (DMC) prior to implementation. Primary analysis will be undertaken on an intention-to-treat basis. Characteristics of participants will be examined by arm. The analysis of the primary endpoints of AET adherence and cancer-specific HRQoL at 18 months will be analysed using logistic and linear regression methods respectively, adjusted for the stratification variables of age, AET type and treatment complexity, as categorised by the computer minimisation algorithm. The size of any intervention effect on each primary outcome over time will be estimated using mixed-effects logistic and linear regression methods (as appropriate), adjusted for stratification variables. Underlying assumptions of the regression models will be investigated, reported and addressed. Different measures of adherence will be considered in sensitivity analyses (e.g. extent of adherence, treating PDC/MARS-5 as continuous variable; early discontinuation, both self-reported and using encashment records; Table 1). Using the encashment data, we will create a longitudinal daily history of AET availability for each trial participant by assigning the days’ supply in each encashed prescription to sequential days from date of randomisation to end of follow-up. This approach takes into account the length of any gaps in medication availability. The full and detailed calculation of this will be detailed within the trial’s Statistical Analysis Plan. A two-sided 5% level of statistical significance will be used throughout.

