***Primary outcomes***	
AET adherence	Combined self-report (Medication Adherence Report Scale (MARS-5)) [31] and Proportion of Days Covered (PDC) calculated from prescription encashment records
Cancer-specific HRQoL	Functional Assessment of Cancer Therapy Scale-General (FACT-G) [32]

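### The 18-month FACT-G regression adjusts for the minimisation factors but not for baseline FACT-G, giving up precision that is available at almost no cost

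*Protocol article*

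**What the plan says.** All references are to the protocol article.

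- **Primary model.** Statistical methods (item 20a) states that adherence and "cancer-specific HRQoL at 18 months will be analysed using logistic and linear regression methods respectively", and that these models are "adjusted for the stratification variables of age, AET type and treatment complexity, as categorised by the computer minimisation algorithm".
- **Model over time.** The same section plans "mixed-effects logistic and linear regression methods (as appropriate), adjusted for stratification variables". Baseline FACT-G is not mentioned here either.
- **Baseline data.** Under Participant timeline (item 13), after consent "participants are asked to complete the baseline questionnaire, consisting of self-reported measures described in Table 1". Table 1 gives FACT-G as the instrument for the HRQoL primary outcome.
- **Order of events.** The same section continues: "Once complete, participants are randomised as described in the Sequence Generation section below". It then says: "All participants are asked to complete a follow-up questionnaire at 6, 12, and 18 months, which repeat the questions from the baseline". The pre-randomisation score is therefore on the same scale as the outcome.
- **Minimisation.** Sequence generation (item 16a) lists two age groups, AET type and five treatment-complexity categories. FACT-G is not among them.
- **Decision rule.** The Outcomes text under Objectives (item 7) requires an effect on both primary outcomes before the intervention is called efficacious.

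**The concern.** A baseline measurement of the outcome is usually among the strongest predictors of its later value. Here it is measured with the same instrument and should be nearly complete, because randomisation follows the baseline questionnaire. It is controlled neither by the allocation scheme nor by the stated model.

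Two things are at stake. The first is precision: outcome variance that baseline could explain stays in the residual, so the confidence interval is wider than it needs to be. The second is chance imbalance: if the arms differ at baseline on FACT-G, part of that difference carries through to the 18-month estimate. Both matter more than usual because success requires FACT-G as well as adherence, so any shortfall in FACT-G power feeds directly into the chance of overall success.

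**Working it through.** **Inputs from the document** (Sample size, item 14, unless noted): 730 randomised per arm; 15% loss, giving 730 × 0.85 = 620.5, stated as 620 analysed per arm; difference of 3 points; SD 15.9; two-sided α = 0.05; 1:1 allocation (item 16a); stated power 91%.

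**Assumed input:** r, the within-arm correlation of baseline with 18-month FACT-G. The document gives no value, so I use 0.3, 0.5 and 0.7.

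**Step 1: reproduce the stated power.**

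SE = 15.9 × √(2/620) = 0.903. The 95% CI half-width is 1.96 × 0.903 = 1.77. Power = Φ(3/0.903 − 1.96) = Φ(1.36) = 0.913.

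This matches the stated 91%, so the sample size uses the marginal SD and takes no credit for baseline adjustment.

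**Step 2: add baseline FACT-G as a covariate.**

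Residual SD = 15.9 × √(1 − r²); SE = residual SD × √(2/620); power = Φ(3/SE − 1.96); equivalent unadjusted n per arm = 620/(1 − r²).

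| r (assumed) | Residual SD | SE | 95% CI half-width | Power for 3 points | Equivalent n per arm |
|---|---|---|---|---|---|
| 0 (no baseline) | 15.90 | 0.903 | 1.77 | 91.3% | 620 |
| 0.3 | 15.17 | 0.861 | 1.69 | 93.6% | 681 |
| 0.5 | 13.77 | 0.782 | 1.53 | 97.0% | 827 |
| 0.7 | 11.35 | 0.645 | 1.26 | 99.6% | 1,216 |

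The reference row has no covariates at all, whereas the planned model already contains three factors. To the extent that those factors explain variance that baseline FACT-G also explains, the gain from adding baseline is smaller than the table shows.

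**Step 3: size of the chance imbalance.** Assume the baseline SD is also 15.9. The between-arm baseline difference then has SE 0.903 and a 95% range of ±1.77 points. With equal SDs, r times that difference carries into an estimate not adjusted for baseline: about ±0.5 points at r = 0.3, ±0.9 at r = 0.5 and ±1.2 at r = 0.7, against a target of 3 points.

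**Step 4: link to the both-outcomes rule.** As an illustration, treat the two tests as independent and use the stated 90% power for adherence. Joint power is 0.90 × 0.913 = 0.82 without baseline and 0.90 × 0.970 = 0.87 at r = 0.5. Independence is my assumption; the document gives no correlation between the two outcomes.

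**The case against.** **Nothing stated is numerically wrong.** A reader might infer that the FACT-G analysis is biased or underpowered. The document does not support that. Under randomisation the planned model is valid, its standard error and 5% test already allow for chance imbalance, and 91% power is reached without baseline adjustment. This objection stands, and it limits the point to efficiency and to the credibility of the single observed estimate.

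**The SAP governs and was not seen.** The section opens by deferring to the analysis plan, and the covariate clause is shared by the logistic and linear models, so an outcome-specific covariate could have been left to the SAP. It would therefore be too strong to conclude that the trial will not adjust for baseline. Even so, the article expressly leaves the detailed PDC calculation to the SAP, whereas it lists the covariates by name. As published, the list omits baseline FACT-G and needs either changing or aligning.

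**The mixed model might use baseline.** Baseline could enter as one of the repeated outcome values, which would recover much of the same information. The text does not say so. It would be wrong to claim that the mixed model discards baseline; it can only be said that no use of it is stated. In any case, the 18-month regression is the primary analysis.

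**The gain may be modest.** Baseline is taken early, up to 14 weeks after the first AET prescription, and for some women around radiotherapy. A low correlation with the 18-month score is therefore plausible, which is why the range starts at 0.3, where the gain is small.

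**Wider changes do not follow.** A reader might extend the point to BCPT and EQ-5D-5L, but the section states no model for them, so there is no stated omission to correct. Moving the primary contrast to the mixed model would be a separate change of estimator. Nor does the point carry over to the adherence composite: its PDC component accrues from randomisation, so the composite has no direct baseline counterpart.

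**Conclusion.** The point holds as a nearly free improvement, not as an error that invalidates the analysis. The stated covariates for the 18-month FACT-G regression and the FACT-G mixed model are the minimisation factors, and baseline FACT-G is omitted although it is available before randomisation.

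The loss is small if r is near 0.3 (about 2 points of power and 0.08 points of CI half-width). It is material if r is 0.5 or more (about 6 points of power or more, and at least 0.24 points of half-width). These figures rest on the stated SD of 15.9, 620 analysed per arm, an assumed r, and a comparison with a model without covariates, so they are upper bounds in the sense given above.

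**What to change.** Before any comparative analysis, add baseline FACT-G total as a continuous covariate, alongside age, AET type and treatment complexity, in the primary 18-month linear regression. State how baseline FACT-G is used in the mixed model as well, whether as a covariate or as one of the repeated measurements. If the SAP already does both, align the protocol text with it.

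The cost is one degree of freedom in the primary regression and a sentence in the plan. No new data are needed. Individual baseline items may be missing even from returned questionnaires; simple imputation of the baseline covariate deals with that. The sample size can stay as it is, since the stated 91% power does not depend on this change.
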